**Methods:**

The KETODOSE trial is a single-center, randomized, double-blind, double-dummy, noninferiority trial conducted at McMaster Children’s Hospital. Eligible participants aged 6 to <18 years with vigorous pain (vNRS >4) are randomized in a 1:1:1 ratio to standard dosing or one of 2 low-dose ketorolac regimens. Study drugs are administered via intravenous push over 5 minutes. Pain scores are assessed at baseline, 30, 60, 90, and 120 minutes. The primary endpoint is the mean change in vNRS score at 60 minutes. Secondary outcomes include pain scores at other time points, time to effective analgesia, rescue analgesia requirements, opioid consumption, and adverse events. Caregiver perceptions regarding analgesic use are evaluated using a mixed-methods semistructured survey. A sample size of 180 participants (60 per group) provides 80% power to detect noninferiority within a margin of 1.0 on the vNRS, assuming an SD of 1.5. Intention-to-treat and per-protocol analyses will be performed.

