#### Primary Hypothesis

Low-dosing strategies will be noninferior to standard dose by a margin of 1.0 on the 11-point vNRS: (1) ketorolac given at 0.5 mg/kg/dose-10 mg will be noninferior to standard dose ketorolac and (2) ketorolac given at 0.25 mg/kg/dose-30 mg will be noninferior to standard dose ketorolac.

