### Primary and Secondary Outcome Measures

#### Primary Objective Endpoint

Between each low-dose ketorolac group (B1 and B2) and the standard group (A) mean differences in pain as measured on vNRS at 60 minutes. We selected 60 minutes postadministration as the time of our primary outcome assessment after careful consideration and in discussion with our parent and youth collaborators and our clinical pharmacologist coinvestigator. This time point (1) allows children to settle from anxiety associated with IV start, which may confound pain assessment; (2) is an acceptable time point for fair assessment of the analgesic effects of the study drug, with a good balance between onset and peak effect for ketorolac; and (3) is a reasonable timeframe for patients to expect relief from vigorous pain.

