### Sample Size Calculations

Based on adult studies [5,9,11,33], we estimated an SD of 1.5 in each group and a mean difference of 0.2. The noninferiority margin of 1.0 is carefully selected to ensure that a rejection of the null hypothesis would: (1) include the effect size that standard dose ketorolac has historically displayed when compared to placebo (relative risk of achieving 50% pain reduction compared to placebo 2.81, 95% CI [1.8-4.4] with number needed to treat of 2.4, 95% CI [1.8, 3.7]), [10] and (2) exclude clinically important levels of inferiority by keeping our margin at 50% of the known MID of 2.0 on the vNRS, ensuring ethical and relevant clinical application. A statistician [name] using nQuery Software (Insightful Science), calculated a total sample size of 171 participants (57/group), which would allow us to test our noninferiority hypothesis using a one-sided alpha of 0.025, 80% power, and a noninferiority margin (Δ) of 1.0. Since our primary outcome is short-term (60 minutes) and we are testing a single dose of ketorolac, we expect very few patients withdrawals or loss to follow-up. However, we will increase our sample size by 5%, to 60 per group (total 180 participants), to account for any unanticipated withdrawals.

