### Analysis Plan

#### (A) Primary Objective Analysis Plan

Data will be described in terms of mean (SD) or 95% confidence limits for normally distributed data and frequency (percentage) in the case of categorical data. The primary endpoint is the difference between the mean reduction in pain scores between each of the low-dose groups (B1, B2) and the standard-dose group (A) 60 minutes post intervention. The primary analysis will include all participants randomized based on the intention to treat analysis and a sensitivity per-protocol analysis will also be performed. A priori, the primary analysis will be adjusted for baseline pain scores using the analysis of covariance (ANCOVA)*.* Generalized estimating equations will be used to examine the impact of baseline pain score on vNRS outcomes across the entire time frame. Noninferiority would be shown if the lower limit of the 95% CI for the between group (groups B1vs A or B2 vs A) differences in the primary endpoint is >1.0. If >5% [34] of our vNRS scores are missing within 120 minutes, we will use multiple imputation to create 5 datasets wherein any missing pain data will be imputed with the Markov chain Monte Carlo method. For secondary endpoints, we will describe those outcomes using descriptive statistics and perform a linear (continuous), logistic, or ordinal regression (categorical or ordinal). If both low-dose strategies are shown to be noninferior to standard dose, we will conduct an exploratory analysis to see if one low-dosing strategy is superior to the other (group B1 vs B2). This will be conducted using ANCOVA to adjust for baseline pain scores and superiority will be determined by a difference that is defined by the MID of 2.0 on the 11-point vNRS. All analyses will be conducted in a blinded fashion. The research pharmacist will provide the trial statistician with anonymized group allocation codes, without revealing the dosing strategies associated with each group. The group identities will remain blinded to the statistician until the first draft of the manuscript with results has been completed. All analyses will be done using SAS (version 9.4; SAS Inc).

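### The primary noninferiority rule lacks a minus sign: with a margin of 1.0, the lower 95% limit for low minus standard dose in pain reduction must exceed -1.0, not 1.0

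*Protocol article*

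**What the plan says.** In the Protocol article, section (A) Primary Objective Analysis Plan, the endpoint is defined as follows: "The primary endpoint is the difference between the mean reduction in pain scores between each of the low-dose groups (B1, B2) and the standard-dose group", at 60 minutes, adjusted for baseline pain by ANCOVA. The decision rule stands in the same paragraph. It opens with "Noninferiority would be shown if the lower limit of the 95% CI for the between group" and then sets a threshold without a minus sign for each low-dose comparison with standard: "groups B1vs A or B2 vs A) differences in the primary endpoint is >1.0".

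The Primary Hypothesis section reads: "Low-dosing strategies will be noninferior to standard dose by a margin of 1.0 on the 11-point vNRS". Sample Size Calculations sizes the trial "using a one-sided alpha of 0.025, 80% power, and a noninferiority margin (Δ) of 1.0" and explains the margin as half the minimally important difference of 2.0, chosen to rule out clinically important inferiority. The Discussion again calls 1.0 the noninferiority margin.

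The outcome is worded in several ways. The Abstract has "The primary endpoint is the mean change in vNRS score at 60 minutes", the Primary Objective Endpoint section has "mean differences in pain as measured on vNRS at 60 minutes", and Table 1 speaks of the pain level at 60 minutes.

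**The concern.** A noninferiority margin is the largest deficit that will be tolerated. On a scale where larger is better, such as pain reduction, the confidence interval for low minus standard must lie wholly above -1.0. The written threshold is +1.0. A rule with that threshold does not test the stated hypothesis and does not go with the stated sample size.

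No other passage gives a confidence-interval criterion, so the error is in the one sentence that decides the primary question. The section also keeps the statistician blinded to the dosing strategy behind each group code until a first manuscript draft exists. An analyst working with coded groups cannot tell from the results that a direction looks wrong, so the written rule has to carry both sign and direction. If the rule is corrected only after results are known, the correction is open to challenge.

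**Working it through.** **Inputs, all from Sample Size Calculations:** "we estimated an SD of 1.5 in each group and a mean difference of 0.2"; one-sided alpha 0.025; power 80%; margin 1.0; 57 per group, raised to 60.

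**1. Reproduce the sample size.** The distance from the assumed deficit to the margin is 1.0 - 0.2 = 0.8.
- Normal approximation: n = 2 × 1.5² × (1.960 + 0.842)² / 0.8² = 55.2, so 56 per group.
- Noncentral t: power is 79.9% at 56 and 80.6% at 57, so 57 per group, as stated.
- Withdrawals: 57 / 0.95 = 60 per group, as stated.

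These figures belong to a test that excludes a 1.0-point deficit, that is, lower limit > -1.0 on the reduction scale.

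**2. Precision at 60 per group.** SE = 1.5 × √(2/60) = 0.274. The 95% half-width is 1.96 × 0.274 = 0.537.

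**3. What each rule requires of the observed difference (low minus standard, reduction).**
- Intended, lower limit > -1.0: observed difference above -1.0 + 0.537 = -0.463.
- As written, lower limit > 1.0: observed difference above 1.0 + 0.537 = 1.537, an advantage of about 1.5 points for the low dose.

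**4. Chance of declaring noninferiority (normal approximation, Φ the normal distribution function, d the true low minus standard difference in reduction).**
- Intended: Φ((d + 1.0)/SE - 1.96).
- Written, natural direction: Φ((d - 1.0)/SE - 1.96).
- Written, opposite direction (standard minus low in reduction, or low minus standard in pain score): Φ((-d - 1.0)/SE - 1.96).

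| True position of the low dose | Intended rule | Written, natural direction | Written, opposite direction |
|---|---|---|---|
| 2.0 worse | about 0 | about 0 | 0.955 |
| 1.0 worse | 0.025 | about 0 | 0.025 |
| 0.2 worse (plan's assumption) | 0.832 | 1.1 × 10⁻¹⁰ | 5.3 × 10⁻⁷ |
| equal | 0.955 | 1 × 10⁻⁸ | 1 × 10⁻⁸ |
| 1.0 better | about 1 | 0.025 | about 0 |
| 2.0 better | about 1 | 0.955 | about 0 |

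In the natural direction the written rule reaches 80% only if the low dose is truly 1.0 + (1.960 + 0.842) × 0.274 = 1.77 points better than standard. By noncentral t the intended rule has 82.6% rather than 83.2% at the plan's assumption; the difference is immaterial.

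**5. Do the different endpoint wordings matter?** Write the ANCOVA as score at 60 minutes = a + b × baseline + g × group. Subtracting baseline from both sides turns b into b - 1 and leaves g unchanged, so score and change from baseline give the same group contrast. Reduction is minus the change and gives -g. The wordings therefore differ only in sign, which decides whether the lower or the upper limit is the relevant one.

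**The case against.** The strongest reply is that any trial statistician would see what was meant. The paragraph speaks of reduction, puts the low-dose groups first in each comparison and uses the lower limit. Together these point to low minus standard with larger meaning better, and so to > -1.0. The hypothesis, the margin's rationale and the one-sided alpha say the same, and 57 per group is reproduced under that test. This stands. A reader might infer that the sign cannot be recovered or that the primary analysis is undefined; the documents do not support that.

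A reader might also infer that the Abstract, the endpoint section, the analysis plan and Table 1 set different primary endpoints. Under the prespecified baseline-adjusted ANCOVA they do not. Only the direction is left to be stated.

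Nor do the documents support giving equal weight to the reading in which an inferior dose is passed as noninferior. It needs either a reversal of the stated comparison order or the pain-score scale used elsewhere in place of the definition in the same paragraph. At the plan's assumed 0.2 deficit its probability is about 5 × 10⁻⁷; it matters only if the low dose is much worse.

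Two limits of the source remain. A statistical analysis plan may exist with a correct rule. A minus sign could also have been lost in typesetting or text extraction, but minus signs survive in the confidence limits quoted in the Discussion, so this is unlikely. Neither limit alters what the article's sentence says.

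**Conclusion.** The decision rule is wrong as written and contradicts the Primary Hypothesis, Sample Size Calculations and Discussion sections. In its natural reading it asks for superiority by more than 1 point and has practically no chance of being met at the plan's assumptions, about 1 × 10⁻¹⁰ against about 83% for the intended rule. The figures assume SD 1.5, a 0.2-point deficit, 60 analysed per group and no gain in precision from baseline adjustment.

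The very small probabilities show how far the sentence is from the design. They are not a forecast of lost power, because the written rule is unlikely to be applied literally. The sample size is sound. This is most likely a drafting slip with a recoverable meaning, but it should be corrected because it is the only explicit criterion for the primary conclusion.

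**What to change.** Replace the rule with, for example: *The treatment effect is the baseline-adjusted (ANCOVA) difference in mean vNRS reduction at 60 minutes, low dose minus standard dose, so that positive values favour the low dose. Noninferiority is shown if the lower limit of the two-sided 95% CI is greater than -1.0.* Add the equivalent on the pain-score scale: upper limit below +1.0 for low minus standard.

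Use that one direction in the Abstract, the Primary Objective Endpoint section, the analysis plan and Table 1, and check that any statistical analysis plan agrees.

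The cost is one sentence and some aligned wording, with no change to sample size or conduct. The article expected analysis to begin in July 2025 and does not show the present status, so the correction should carry a date and say whether it preceded unblinding. If it did not, the report should state that and point to the margin, hypothesis and sample size as the prespecified basis for -1.0.

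### Five imputed datasets leave avoidable random-seed noise in a borderline primary noninferiority verdict, if imputation is triggered

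*Protocol article*

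**What the plan says.** All of the following stands in the Protocol article under Analysis Plan, (A) Primary Objective Analysis Plan, unless noted.

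- Population: "The primary analysis will include all participants randomized based on the intention to treat analysis". The model is an ANCOVA with baseline pain score as covariate.
- Decision: "Noninferiority would be shown if the lower limit of the 95% CI for the between group" clears the 1.0 margin, for B1 against A and for B2 against A.
- Trigger: "If >5% [34] of our vNRS scores are missing within 120 minutes". This pools the scores over time points; it is not a rule about the 60-minute score alone.
- Action: "we will use multiple imputation to create 5 datasets wherein any missing pain data will be imputed with the Markov chain Monte Carlo method".
- Design values, under Sample Size Calculations: "we estimated an SD of 1.5 in each group and a mean difference of 0.2", tested "using a one-sided alpha of 0.025, 80% power, and a noninferiority margin (Δ) of 1.0". This gives 57 per group, raised to 60. No missing-data rate is stated; the section says only that few withdrawals are expected.

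**The concern.** The number of imputations is written into the plan, so this is a stated choice and not a detail left for later. When the trigger is met, the imputed 60-minute scores enter the primary confidence limit. That limit then carries simulation noise from two sources: the pooled estimate, and the between-imputation variance, which five datasets estimate on 4 degrees of freedom.

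The verdict is a hard yes or no at the margin. When the limit lies close to the margin, two equally proper runs on the same trial data can give opposite answers. A conclusion about lower-dose ketorolac in children should not turn on a random seed when the noise can be reduced at almost no cost.

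**Working it through.** **1. The plan's own sample size.** The normal approximation gives n = 2 × 1.5² × (1.960 + 0.842)² / (1.0 − 0.2)² = 4.5 × 7.85 / 0.64 = 55.2, so 56 per group. The noncentral-t version gives 57 (power 80.6%), as stated. Allowing for 5% loss, 57 / 0.95 = 60. The design inputs therefore reproduce.

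**2. Where the limit sits.** On the pain-reduction scale, the margin as the sample size section intends it means a lower limit above −1.0. With 60 per arm and complete data, SE = √(2 × 1.5² / 60) = √0.075 = 0.274. The lower limit averages −0.2 − 1.98 × 0.274 = −0.742. That is 0.258 above the margin, or 0.94 SE. The density of the limit at the margin is φ(0.94) / 0.274 = 0.256 / 0.274 ≈ 0.935 per vNRS point.

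**3. Size of the noise.** Assumptions, because the plan gives no figures: a share p of 60-minute scores is missing completely at random, and the child's other scores explain a fraction R² of a missing score.

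- Fraction of missing information: FMI = p × (1 − R²)
- Variance: V = 0.075 / (1 − FMI)
- Between-imputation variance: B = FMI × V
- Monte Carlo SD of the estimate: √(B/m), with m the number of imputations

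At p = 10% and R² = 0: V = 0.0833 (SE 0.289) and B = 0.00833. The Monte Carlo SD is √(0.00833/5) = 0.041 with 5 imputations and √(0.00833/50) = 0.013 with 50. The ratio is √10, about threefold.

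**4. Chance that two seeds disagree, one contrast, from this model.** Estimate and B were redrawn for two independent seeds, with Rubin's total variance, at SD 1.5, true difference 0.2 and R² from 0.4 to 0.

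| 60-minute scores missing | m = 5 | m = 50 |
|---|---|---|
| 5% | 2.5–3.5% | 0.8–1.0% |
| 10% | 3.9–5.8% | 1.1–1.7% |

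At 2–3% missing with m = 5, the rate is about 1.5–2.5%.

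**5. Full simulation as a second method.** Here 6,000 trials per scenario were generated, with Bayesian normal imputation, ANCOVA, Rubin's rules and Barnard-Rubin degrees of freedom. Each trial was imputed twice with independent seeds.

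| Assumed structure (m = 5) | 3% missing | 5% missing | 10% missing |
|---|---|---|---|
| No baseline correlation | 2.6% | 3.4% | 6.1% |
| Baseline correlation 0.5 | 1.4% | 2.1% | 4.2% |
| Baseline correlation 0.3 plus an informative auxiliary score | 1.4% | 2.2% | 3.6% |

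Over the same three structures, m = 20 gives 1.0–1.9% at 5% missing and 1.7–2.7% at 10%. With m = 100 the rates are 0.4–0.8% and 0.7–0.9%.

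Hand check of the first row: the expected gap between two runs is 1.128 × s, where s is the Monte Carlo SD of the limit (0.033 at 5% missing, 0.053 at 10%). Then 0.935 × 1.128 × 0.033 = 3.5% and 0.935 × 1.128 × 0.053 = 5.6%, close to 3.4% and 6.1%.

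**6. Dependence on the true difference** (no baseline correlation, m = 5, at 5% and 10% missing): a difference of 0 gives 1.4% and 3.0%; a difference of 0.5 gives 5.1% and 7.6%.

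**7. Power.** In the same simulation without baseline correlation, m = 5 against m = 100 gives 79.6% against 80.0% at 5% missing, and 77.5% against 78.7% at 10%.

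**The case against.** Nothing is statistically wrong with five imputations. Rubin's rules already carry the finite-m term, and in the model of step 3, with the true difference placed at the margin, the false noninferiority rate stays at about 2.5%. The noise (0.041) is about one-seventh of the sampling SE (0.289), so only a limit already close to the margin can flip. All of this stands. A reader might infer that five imputations bias the result or inflate the error rate; neither the plan nor the calculation supports that.

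A reader might also infer that the primary verdict depends on the seed in some fixed share of trials, such as 1 in 20 to 1 in 40. The document does not support an unconditional rate:

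- Few withdrawals are expected, and without the trigger no imputation reaches the primary limit.
- The trigger pools scores to 120 minutes, so it can fire with fewer than 5% of 60-minute scores missing.
- The upper ends assume that the child's other scores say nothing about the missing one.
- Baseline adjustment may reduce the SD. A residual SD of 1.3 (1.5 × √(1 − 0.5²), an assumed baseline correlation of 0.5) lowers the model's rates to 1.5–2.1% at 5% missing and 2.4–3.5% at 10%.

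Finally, a seed may be fixed in an analysis plan that is not shown, so its absence is no defect. A fixed seed makes one run repeatable, but the verdict it repeats still carries the noise of five imputations. That noise follows from the stated number, and this part of the point remains.

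**Conclusion.** The point holds as a minor, conditional one. If imputation is triggered and 5–10% of 60-minute scores are missing, the verdict for one contrast would differ between two seeds in roughly 2–6% of such trials, at SD 1.5, a true difference of 0.2 and 60 per arm. Two different methods agree on that order of size. The missing share, the missing-completely-at-random mechanism and the correlations among scores are assumptions. There are two primary contrasts, so the chance that at least one is affected is no smaller than the figure for one. What is at stake is the reproducibility of a close result; validity is not in question, and the power cost is at most about 1 percentage point at 5–10% missing.

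**What to change.** In the Primary Objective Analysis Plan, replace the five imputed datasets with a larger prespecified number, for example at least 50. By the model above this lowers two-seed disagreement to about 1–2% at 5–10% missing; 20 would achieve part of the gain and 100 somewhat more. There is no sharp threshold, so the number is a judgement, but it should be set before the data are analysed. Recording the seed in advance also rules out a choice among runs. The cost is one changed number and a negligible amount of computing for 180 children with a few scores each; no additional data or participants are needed.

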#### Secondary Hypothesis

Dosing at 0.5 mg/kg/dose-10 mg will be superior to 0.25 mg/kg/dose-30 mg by the minimally important difference (MID) of 2.0 on the 11-point vNRS.

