## Discussion

The KETODOSE trial addresses a critical evidence gap in determining optimal ketorolac dosing for common acute pain indications in the ED, where current practices have relied largely on adult data and expert opinion. Should our findings demonstrate that lower-dose regimens (0.25 mg/kg up to 30 mg and 0.5 mg/kg up to 10 mg) are noninferior to standard dosing, this would provide the first high-quality evidence to support dose de-escalation in children with acute pain. Such findings could validate the common, but unproven, practice of using a 10 mg ceiling dose in children. Moreover, this trial tests whether ceiling dose or per-kilogram dosing is the driver of analgesic effectiveness. If 0.5 mg/kg up to a maximum of 10 mg is found to be noninferior to the standard 0.5 mg/kg up to 30 mg regimen, yet superior to 0.25 mg/kg up to 30 mg by the MID, this would suggest that a higher per-kilogram dose combined with a lower ceiling dose may represent the optimal ketorolac strategy for children, balancing efficacy with reduced drug exposure.

In preparation for this trial, we conducted and published [48] a systematic review and meta-analysis of 4 databases and trial registries in early 2022 to identify any RCTs regarding ketorolac dosing. We identified four RCTs that included 392 adult participants. Studies compared standard dose ketorolac (30 mg) to either mid-dose ketorolac (15-20 mg) or low-dose ketorolac (10 mg). Most trials had small sample sizes and used a single dose of IV ketorolac [5,9,11], with the exception of one study that used intramuscular ketorolac.[33] All trials used the 100-mm visual analogue scale to measure their primary outcome pain level at 1 hour (3 trials) or 4 hours (1 trial) [11] postintervention. Four trials with 196 participants compared IV ketorolac 30 mg to 15-20 mg, with a nonsignificant mean difference of 1.03 mm (95% CI –2.45 to 4.5). Two trials with 116 participants compared ketorolac 30 mg to 10 mg and found a nonsignificant mean difference of 1.55 mm (95% CI –2.42 to 5.53) favoring the 30 mg dose. There was consistency across all trials and an *I*^2^ of 0%. This suggests that, for adults with acute pain, there is no clinically or statistically meaningful difference between lower doses of ketorolac and standard doses, and that an analgesic ceiling to ketorolac is reached at 10 mg in adults. However, there were no published pediatric trials or registered ongoing trials on trial registries.

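### The condition that both low doses be noninferior makes the 2.0-point secondary hypothesis (B1 better than B2) practically untestable

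*Protocol article*

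**What the plan says.** Arms: A is 0.5 mg/kg capped at 30 mg (standard), B1 is 0.5 mg/kg capped at 10 mg, and B2 is 0.25 mg/kg capped at 30 mg.

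- The Secondary Hypothesis section, like the abstract's Objective, states without condition that B1 "will be superior to 0.25 mg/kg/dose-30 mg by the minimally important difference (MID) of 2.0" points.
- The Primary Objective Analysis Plan makes the comparison conditional and calls it exploratory: "If both low-dose strategies are shown to be noninferior to standard dose, we will conduct an exploratory analysis". The criterion is that "superiority will be determined by a difference that is defined by the MID of 2.0 on the 11-point vNRS". It does not say whether 2.0 applies to the point estimate or to a confidence limit.
- The Discussion describes the informative outcome as B1 noninferior to A, "yet superior to 0.25 mg/kg up to 30 mg by the MID". It does not ask that B2 be noninferior as well.
- The Primary Hypothesis section sets the margin: "Low-dosing strategies will be noninferior to standard dose by a margin of 1.0 on the 11-point vNRS".

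Table 1 lists no B1-versus-B2 superiority contrast on the pain score, so the conditional sentence in the analysis plan is the only analysis given for this hypothesis.

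**The concern.** The condition asks that B2 be close to A. The criterion asks that B1 be far ahead of B2. Together they push B1 well above the standard dose. Yet the hypothesis and the Discussion are about something else: B1 about as good as A, and B2 clearly worse. In that situation B2 should fail noninferiority, and the stated rule then does not call for the comparison.

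At stake is the question, raised in the Discussion, of whether the ceiling or the per-kilogram dose drives the effect. If B2 fails, following the analysis plan leaves the Discussion's conclusion without its planned test. Running the test anyway departs from the plan. The contrast also has two statuses, secondary hypothesis and exploratory analysis.

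**Working it through.** **Inputs.** From Sample Size Calculations: "we estimated an SD of 1.5 in each group and a mean difference of 0.2"; "using a one-sided alpha of 0.025, 80% power, and a noninferiority margin (Δ) of 1.0"; 57 per group, raised to 60 for 5% withdrawals. From the analysis plan: a 95% CI for noninferiority and a 2.0-point criterion for B1 versus B2. Differences below are in pain reduction, so higher is better. The noninferiority limit is printed there as above 1.0; I read it as above -1.0, in line with the Primary Hypothesis.

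**The plan's own sample size.** Normal approximation: n = 2 × 1.5² × (1.96 + 0.842)² / (1.0 - 0.2)² = 55.2, so 56 per group. With the noncentral t distribution, power is 0.799 at 56 and 0.806 at 57, which gives the stated 57. Then 57 / 0.95 = 60. The design figures are reproduced.

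**Joint conditions, observed differences.**

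1. SE of a difference = 1.5 × √(2/60) = 0.274. Half-width h = 1.96 × 0.274 = 0.537.
2. B2 is noninferior if (B2 - A) - h > -1.0, that is, observed B2 - A > -0.463.
3. B1 - A = (B1 - B2) + (B2 - A). If B1 - B2 is at least 2.0, then B1 - A > 2.0 - 0.463 = 1.537.
4. If instead the lower 95% limit of B1 - B2 must exceed 2.0, then B1 - A > 1.537 + 0.537 = 2.074.

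In general the requirement is B1 - A > 1 + h on the point-estimate reading. Baseline adjustment would shrink h, but the requirement stays above 1.0. With 57 per arm, SE = 0.281 and the figure is 1.551.

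**Joint conditions, true means.** If B1 is no better than A and B2 is less than 1.0 worse than A, then B1 - B2 is below 1.0, half of what is required.

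**Simulation.** 1,000,000 runs per row, three independent arm means, 60 per arm, SD 1.5, no baseline adjustment. Entries are probabilities.

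| True B1 - A, B2 - A | Both noninferior | Both noninferior and observed B1 - B2 ≥ 2.0 | Only B1 required noninferior: observed B1 - B2 ≥ 2.0 | Only B1 required noninferior: lower limit > 2.0 |
|---|---|---|---|---|
| 0, 0 | 0.921 | 0 | 0 | 0 |
| -0.2, -0.2 (planning value) | 0.731 | 0 | 0 | 0 |
| 0, -0.5 | 0.442 | 0 | 0 | 0 |
| 0, -1.0 | 0.025 | 0 | 0.0002 | 0 |
| 0, -2.0 | 0 | 0 | 0.495 | 0.025 |
| 0, -2.5 | 0 | 0 | 0.929 | 0.443 |
| 0, -3.0 | 0 | 0 | 0.955 | 0.920 |
| +1.0, -1.0 | 0.025 | 0.002 | 0.501 | 0.025 |
| +2.5, 0 | 0.955 | 0.921 | 0.966 | 0.446 |

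A zero means no run out of 1,000,000. The zeros in the third column follow from the algebra once B1 is no better than A; they illustrate it and are not separate evidence. The last row shows that both conditions can be met together if B1 is far better than A.

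**Can B1 be far better than A?** Under the Interventions section, B1 has A's mg/kg dose with a lower ceiling. At 20 kg both give 10 mg; at 60 kg A gives 30 mg and B1 gives 10 mg. B1 never gives more drug than A at any weight.

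**The case against.** Five points can be made for the plan.

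- **A reader might infer that the two conditions exclude each other, so that the hypothesis can never be supported.** The document does not support that. Noninferiority is one-sided, and nothing limits how far B1 may exceed A. With B1 truly 2.5 points better than A and B2 equal to A, both conditions are met in 92% of runs. What rules this out in practice is a non-decreasing dose response, which is a reasonable assumption but not one the document states.
- **The condition has a sensible use.** Choosing between two regimens once both are acceptable is a legitimate exploratory question. That stands. But it is not the directional hypothesis in the Secondary Hypothesis section, nor the case described in the Discussion.
- **A 2.0-point gap is unlikely with or without the condition.** Planning assumed a difference of 0.2. The adult trials comparing 30 mg with 10 mg differed by 1.55 mm on a 100-mm scale, or 0.155 points if rescaled to 0-10. Under the dosing rules B1 and B2 both give 10 mg at 40 kg, and above that weight B2 gives more drug. This stands, so the practical loss should not be read off the rows where B2 is 2 to 3 points worse. It does not reconcile the passages.
- **The text does not forbid reporting the contrast otherwise.** Correct, and each low dose is compared with A in any case. But no other analysis of the hypothesis is stated, so a result reported after B2 fails would be outside the plan.
- **The primary conclusions are untouched.** Correct: the noninferiority tests, the sample size and their error rate do not depend on this contrast.

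**Conclusion.** The point holds in a limited form. Under the stated condition, the B1-versus-B2 hypothesis can be supported only if B1 beats the standard arm by more than about 1.54 points observed, or about 2.07 if 2.0 applies to the lower confidence limit. In true means the figure is more than 1.0. Assuming that more drug never gives less relief, the hypothesis is practically untestable. In the situation the Discussion wants to interpret, with B1 equal to A and B2 worse by 2.0 or more, both arms passed noninferiority in none of 1,000,000 runs. With B2 worse by 2.5 and no condition on B2, the 2.0-point criterion would be met together with B1 noninferiority in 93% of runs (point estimate) or 44% (confidence limit).

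This rests on SD 1.5, 60 analysed per arm, no gain from baseline adjustment, and the noninferiority limit read as above -1.0. It should be fixed because the sections contradict one another on a stated hypothesis. It does not threaten the primary result.

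**What to change.** 1. In the Primary Objective Analysis Plan, remove the requirement that B2 be noninferior before B1 and B2 are compared. Either drop the condition altogether or require noninferiority of B1 only.
2. Report the baseline-adjusted ANCOVA difference B1 - B2 with its 95% CI, and state where it lies relative to 0 and to 2.0.
3. Keep 2.0 as the criterion for the stated hypothesis. Replacing it with a test against 0 would answer a different, weaker question. Say whether 2.0 applies to the point estimate or to the confidence limit; the probabilities above show how much this matters.
4. Give the contrast one label, secondary or exploratory, in the abstract, the Secondary Hypothesis, the analysis plan and the Discussion.
5. Date the change and document that it was made before unblinding and before any coded group comparison was seen. The article reports 170 of 180 participants enrolled by April 2025 and analysis from July 2025, so timing matters. If results have already been seen, call the change post hoc.

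Cost: wording only, since the contrast uses the same ANCOVA approach and the same data. The downside is one more reported comparison outside the primary error rate.
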